**Methods/design:**

Fifty patients will be included in a randomized controlled trial. Patients scheduled for TKA with clinical and radiological signs of femorotibial and patellofemoral OA will be included. Arthritis of the patellofemoral joint was determined based on the preoperative Baldini and Merchant X-ray views, which is assessed by the orthopaedic surgeon who treats the patient. Exclusion criteria are rheumatoid arthritis, history of patellar fracture, tuberosity transposition, high tibial osteotomy (HTO), hip arthroplasty and posterior cruciate ligament insufficiency. Patients will be randomized to undergo TKA either with or without patellar resurfacing. Outcomes will be assessed preoperatively, at 6 weeks and at 6, 12, 18 and 24 months postoperatively. Primary outcome measure is the patellofemoral scoring system according to Baldini. Secondary outcome measures are the Knee Society clinical rating system (KSS) and the Knee Osteoarthritis Outcome Scale (KOOS) scores. Conventional weight-bearing radiographs, and views according to Baldini will be used to asses component loosening, wear, and patellofemoral problems including fracture or loosening of resurfaced patellae, subluxation and wear of non-resurfaced patellae.

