### Sample size calculation

Using the patellofemoral scoring system by Baldini et al.[30], the sample size is based on a mean difference of 10 points between both groups at 2-years follow-up. To detect this difference of 10 points with a standard deviation of 8 points, alpha of 5% and a power of 90%, a sample size of 18 patients in each study group is required. To compensate for potential drop-out and loss to follow-up, a total of 50 patients will be included in the study.

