### Statistical analysis

All statistical analyses will be computed using SPSS (IBM SPSS, Inc., Version 20.0, 2011). For the clinical parameters, t-tests will be used for continuous variables or the Mann–Whitney U-test when the variables are not normally distributed. A Chi-square test will be used for dichotomous variables. To assess differences in the results of the Baldini score and the KOOS over time between the two study groups, generalised estimating equations (GEE) analyses will be conducted. Longitudinal data are characterised by repeated observations of the same subjects. GEE analysis was developed to correct for repeated outcomes within the same subject[36]. With a GEE analysis, adjustments for the effect of differences in patient characteristics on the outcome variables can also be made by including these variables as covariates. Both an intention-to-treat analysis as a per-protocol analysis will be performed.

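### GEE in 36 to 50 patients with no stated small-sample correction: the 24-month test becomes mildly liberal (about 6-7%), and an omnibus group-by-visit test, if used, clearly liberal (about 10.5-13.4%)

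*Protocol article*

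**What the plan says.** The Statistical analysis section of the protocol article names GEE as the method for between-arm differences over time in the Baldini score (the primary outcome) and the KOOS, run in SPSS 20. It gives two reasons. One is that "GEE analysis was developed to correct for repeated outcomes within the same subject"; the other is that covariates can be included. It does not state the coding of time, the working correlation, the covariance estimator or the reference distribution, and it does not mention the small number of patients. The same section gives t-tests or Mann-Whitney tests for continuous clinical parameters.

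On the schedule, the abstract says: "Outcomes will be assessed preoperatively, at 6 weeks and at 6, 12, 18 and 24 months postoperatively". That makes six visits, five of them postoperative.

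The Sample size calculation rests on "a mean difference of 10 points between both groups at 2-years follow-up" "with a standard deviation of 8 points", and concludes that "a sample size of 18 patients in each study group is required". It then adds: "To compensate for potential drop-out and loss to follow-up, a total of 50 patients will be included in the study". The hypothesis in the Background is also a 24-month comparison.

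**The concern.** In GEE the independent units are patients, here 36 to 50. The usual sandwich variance is biased downwards with so few units, and the usual Wald test refers it to a normal or chi-square distribution as if it were known. Both faults make p-values too small and intervals too narrow, and the effect grows with the degrees of freedom of the test. A comparison over six visits with visit as a factor has 5.

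At stake is whether tests on the primary score keep the 5% level that the sample size section assumes.

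A secondary matter is loss to follow-up. Unweighted GEE in general needs loss to be unrelated to observed scores beyond the modelled covariates. A likelihood-based mixed model remains valid if loss depends on earlier observed scores, provided the model is right.

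**Working it through.** **Inputs.** Required n = 18 per arm and total 50, so 25 per arm (Sample size calculation); 1:1 allocation (Randomization); six visits (Data collection methods); alpha 5%, taken as two-sided. Room for loss: (50 - 36)/50 = 28%.

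**The plan's own figure.** For a difference of 10, SD 8, alpha 5% and power 90%:

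n = 2(1.960 + 1.282)² × 64/100 = 13.4, so 14 per arm, or 15 with the noncentral t.

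The stated 18 is therefore not reproduced. It is larger than its inputs need (power about 95-96% at 18), so the discrepancy is conservative. It does not bear on this point; 18 is used below only as the lower end of the evaluable number.

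**Assumptions where the protocol is silent.** Visit as a factor, identity link, uncorrected sandwich variance, chi-square reference, normal data, complete follow-up.

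**Formula.** With n per arm, a saturated group-by-visit mean and a p-df contrast, the robust Wald statistic equals Hotelling's T² × n/(n - 1). With N = 2n - 2, the true rejection rate at nominal 5% is

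P[ F(p, N - p + 1) > χ²₀.₉₅(p) × ((n - 1)/n) × (N - p + 1)/(N p) ].

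**Example, n = 25, p = 5.** N = 48 and N - p + 1 = 44. The threshold is 11.0705 × 0.96 × 44/240 = 1.948, and P[F(5, 44) > 1.948] = 0.1055.

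**Example, n = 18, p = 5.** N = 34 and N - p + 1 = 30. The threshold is 11.0705 × (17/18) × 30/170 = 1.845, and P[F(5, 30) > 1.845] = 0.1341.

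| Test | 25 per arm | 18 per arm |
|---|---|---|
| Group by visit, six visits (5 df) | 0.1055 | 0.1341 |
| Group by visit, five postoperative visits (4 df) | 0.0920 | 0.1127 |
| 24-month contrast (1 df) | 0.0608 | 0.0653 |

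**Confidence interval at 24 months.** The ratio of its width to the t interval is 1.96 × √((n - 1)/n)/t(2n - 2):

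- n = 25: 1.96 × √(24/25)/2.011 = 0.955, so 4.5% too narrow; coverage 93.9%.
- n = 18: 1.96 × √(17/18)/2.032 = 0.937, so 6.3% too narrow; coverage 93.5%.

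**Simulation.**

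- Repeated draws of 20,000 data sets, with exchangeable or AR(1) correlation, agreed with the formula. Skewed data gave 12.6% (18 per arm) and 9.8% (25 per arm) for the 5-df test.
- With 25 per arm and 28% random dropout, the 5-df test rejected at 11.7% to 12.3% and the 24-month contrast at 7.0% to 7.2%.
- With time as a linear trend, the 1-df interaction rejected at 5.3% to 6.4%.

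**Does the alternative work?** A REML random-intercept model with an F test of group by visit rejected at 4.8% (18 per arm), 4.9% (25 per arm) and 4.8% (25 per arm with 28% dropout) when that covariance form was true. Fitted to AR(1)-type data with 28% dropout, it rejected at 7.6%. The exact small-sample F for an unstructured covariance with complete data gave 4.9% to 5.2% over six visits. An unstructured mixed model with dropout was not simulated.

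**The case against.** The strongest objection is that the inflation attaches to choices the protocol does not make. The article says only that GEE will be used. An unseen analysis plan could add a bias correction, code time linearly, or take a single average group effect, which is a 1-df contrast. The 10.5% to 13.4% range is the top of what the text allows. This stands: the range must be stated as conditional. What remains is that the protocol itself chooses a large-sample method for a small trial and gives no sign of having considered the number of patients. Every factor-coded reading without a correction is liberal to some degree.

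A reader might infer that the primary test runs at about twice 5%. The documents do not support that. The stated 5% belongs to the 24-month difference, for which the inflation is to 6.1-6.5%, or about 7% with dropout. The protocol never ties an omnibus test to the hypothesis or the sample size. The t-test sentence could even be read to cover the 24-month Baldini comparison, in which case the problem would not arise there.

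A reader might also infer that dropout will bias the GEE estimates. That is plausible over 24 months, but the documents give no expected loss rate and no link between loss and scores. The 28% is only the gap between 36 and 50, and the size of any bias cannot be computed.

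Finally, the KSS is taken at the same visits but is not in the GEE sentence. Reading this as ten separate tests (two scores at five postoperative visits) is an inference; the text does not say it.

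**Conclusion.** The point holds in a limited form. GEE is fixed for the primary score with 36 to 50 patients and no correction is named. If the usual uncorrected sandwich variance and chi-square references are used:

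- an omnibus group-by-visit test with visit as a factor has a real error rate of about 10.5% to 13.4% over six visits, or 9.2% to 11.3% over the five postoperative ones;
- the 24-month contrast is only mildly liberal, with coverage of about 94% on complete data;
- a linear time trend is nearly unaffected.

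The figures for complete data are exact under normality and were supported by simulation. They depend on time coding and an estimator that the protocol leaves open. The change is worth making because it is cheap and concerns the primary outcome. The main 24-month conclusion is not thereby shown to be unsound.

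**What to change.** Analyse the Baldini score and the KOOS with a REML linear mixed model for repeated measures. Use visit as a factor, an unstructured or otherwise adequate covariance (not a random intercept alone), and Satterthwaite, Kenward-Roger or similar small-sample degrees of freedom. Name the 24-month arm contrast as the primary test.

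Alternatively, keep GEE and specify a bias-corrected sandwich with t or F references. This repairs the error rate but does not give the mixed model's tolerance of loss that depends on earlier observed scores.

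Putting the KSS in the same model is an optional step for consistency.

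The cost is one changed analysis procedure, no new data, slightly wider intervals and reliance on a modelled covariance. Unstructured over six visits, that covariance has 6 × 7/2 = 21 parameters to estimate from 36 to 50 patients, so a fallback structure should be named in advance. Whether SPSS 20 offers the chosen correction should be checked before it is written in.

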## Methods and design

### Study design

The study design is a randomized controlled trial: patients will be randomly allocated to have TKA with or without patellar resurfacing. The study will be conducted at the Department of Orthopaedic Surgery of Martini Hospital Groningen, the Netherlands, a secondary referral teaching hospital. One investigator will enroll the patients. Two orthopaedic surgeons will perform the procedure, and are thus not blinded. One independent investigator, not involved with enrollment or surgical procedure, will evaluate the outcome measurements. This investigator and all patients will remain blinded through the assigned regimen. The study has been approved by a Medical Ethics Committee, and is also registered in the Netherlands Trial Registry [Reference NTRTC3108].

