### Main study parameter/endpoint

Primary outcome measure is the patellofemoral scoring system by Baldini et al. This tool represents patellofemoral kinematics more accurately, and may explain related patellofemoral complaints better[30]. The scoring system includes objective and subjective aspects concerning the patellofemoral joint, ranging from 0 (worst) to 100 (best)[30].

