**Flowchart of patient inclusion.**

### Data collection methods

Preoperatively as well as at six weeks, and six, 12,18 and 24 months postoperatively patient assessments will be performed. Age, gender, body mass index (BMI), severity of OA, will be recorded preoperatively. Perioperative complications will be registered. Primary and secondary outcome measurements will be obtained at all time points by an independent investigator (Table 1).

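### The planned GEE does not commit to adjusting for the preoperative value of the analysed score, which forgoes precision and leaves the choice between adjusted and unadjusted estimates open

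*Protocol article*

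**What the plan says.** Under Main study parameter/endpoint, "Primary outcome measure is the patellofemoral scoring system by Baldini et al". Under Data collection methods, "Preoperatively as well as at six weeks, and six, 12,18 and 24 months postoperatively patient assessments will be performed", and "Primary and secondary outcome measurements will be obtained at all time points by an independent investigator". Table 1 confirms that the Baldini score, KOOS and KSS are all scheduled at day 0. The same section states: "Age, gender, body mass index (BMI), severity of OA, will be recorded preoperatively".

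The Statistical analysis section names the longitudinal model: "To assess differences in the results of the Baldini score and the KOOS over time between the two study groups, generalised estimating equations (GEE) analyses". After a short explanation of what GEE does, it adds that "adjustments for the effect of differences in patient characteristics on the outcome variables can also be made by including these variables as covariates". It gives no list of covariates and does not say which model, with or without covariates, carries the main conclusion. Nor does it say whether the preoperative score is a covariate, a response at time 0 or unused.

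Under Sample size calculation, "the sample size is based on a mean difference of 10 points between both groups at 2-years follow-up". That calculation is a plain two-group comparison with no baseline correlation in it. The Randomization section describes computer-generated 1:1 allocation and mentions no stratification.

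**The concern.** For a score measured before and after surgery, the preoperative value is normally the first candidate for a prognostic covariate. Here it is already being collected. The article takes up the subject of adjustment but words it as a possibility, and in terms of patient characteristics in general.

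Two things follow in a trial of this size. First, precision is left unused. In any one trial, a chance difference between the arms in preoperative score also carries over into an unadjusted 24-month difference. Secondly, the analyst will hold an unadjusted and an adjusted estimate with nothing in this text to say which one is the result.

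**Working it through.** **Inputs.** From Sample size calculation: difference 10 points, SD 8, alpha 5%, power 90%, 18 per group required, 50 patients in total (25 per arm at 1:1). Two assumptions are mine: a two-sided test, since sidedness is not stated, and a correlation ρ of 0.3 to 0.5 between the preoperative and 24-month scores.

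**1. The plan's own figure.** n per group = 2 × (1.960 + 1.282)² × 8² / 10² = 13.45, so 14 by the normal approximation and 15 by the t-test. The stated 18 is not reproduced. It is on the safe side, and is a separate matter from this point. With 18 per group the t-test has 95.4% power for 10 points.

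**2. Residual variance.** Adjusting for a baseline value multiplies the variance by 1 − ρ².
- ρ = 0.3: 0.91, a cut of 9%, worth 1/0.91 = 1.10, or about 10% more patients.
- ρ = 0.5: 0.75, a cut of 25%, worth 1/0.75 = 1.33, or about 33% more patients.

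**3. Confidence interval half-width at 24 months**, t × 8 × √(1 − ρ²) × √(2/n):

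| Per arm | Unadjusted | ρ = 0.3 | ρ = 0.5 |
|---|---|---|---|
| 18 (t = 2.032 unadjusted, 2.035 adjusted) | 5.42 | 5.18 | 4.70 |
| 25 (t = 2.011 unadjusted, 2.012 adjusted) | 4.55 | 4.34 | 3.94 |

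**4. Power at 18 per arm.** For 10 points it goes from 95.4% to 96.8% (ρ = 0.3) or 98.8% (ρ = 0.5). For a 6-point difference, taken only as an illustration, it goes from 59% to 63% or 71%.

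**5. Effect of a chance imbalance.** If the arms differ at baseline by 2 standard errors, the unadjusted 24-month difference shifts by ρ × 2 × 8 × √(2/25) = ρ × 4.53. That is 1.36 points at ρ = 0.3 and 2.26 points at ρ = 0.5, or 30% to 50% of the 4.55-point significance threshold at 25 per arm. An imbalance that large arises by chance in about 5% of trials.

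**6. What an open choice permits.** A null simulation of a single-visit comparison was run with 18 per arm (8000 runs, nominal 5%). The unadjusted test alone and the baseline-adjusted test alone each held about 5%. Reporting whichever of the two had the smaller p-value gave 6.3% at ρ = 0.3 and 7.5% at ρ = 0.5. Adjusting only when the baseline scores differed at p < 0.05 gave 4.6% and 4.5%, so that rule did not inflate the error rate.

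**The case against.** The strongest reply is that this is a condensed article, that a covariate list is commonly left to an analysis plan, and that the sentence on adjustment only describes what GEE can do. That is right as far as a full covariate list goes. It does not dispose of the point. The article does address adjustment, does so permissively, and leaves the most useful available variable without a role. Naming it is a concrete improvement using data already collected.

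The reply is also right that the stakes are moderate. Every gain above depends on an assumed correlation, the 10-point target is well powered without adjustment, and the imbalance in step 5 is uncommon. The error rates of 6.3% and 7.5% describe deliberate selection by result, which the article does not propose.

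A reader might infer four stronger charges that the text does not support.
- **Covariates are chosen because the arms turn out to differ.** The wording sets no baseline test and no trigger. It can equally mean patient differences that affect the outcome. Step 6 also shows that a significance trigger on the baseline score would not raise the error rate.
- **The group effect is diluted by the preoperative visit.** This needs that visit to be a response and the test to be a single group effect averaged over visits. The article states neither, and a comparison over time fits a group-by-time model just as well.
- **The main analysis is an unadjusted t-test.** The t-tests are assigned to the clinical parameters, and GEE to the Baldini score and the KOOS. Nothing makes a t-test primary.
- **Surgeon must be a covariate.** The article says "Two orthopaedic surgeons will perform the procedure, and are thus not blinded", but states no stratification by surgeon and gives nothing that makes the term necessary. Including it is a preference.

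**Conclusion.** The point holds in a limited form. The planned GEE does not commit to adjusting for the preoperative value of the score being analysed, although that value is to be collected in every patient. For ρ between 0.3 and 0.5 the loss is 9% to 25% of residual variance. At 18 per arm that is a half-width of 5.4 points where 5.2 to 4.7 was available. Power for the 10-point difference is not in question. What is lost is interval width, power for smaller differences, protection against chance imbalance, and a settled answer on which estimate is the result.

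The conclusion rests on the assumed correlation, an SD of 8, a two-sided 5% test and a calculation at the single 24-month visit. The whole GEE was not simulated. Some of the baseline information would be recovered if the preoperative score entered the model as a repeated response, which the article neither states nor excludes.

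**What to change.** State in the Statistical analysis section that the primary GEE includes the preoperative value of the analysed score as a pre-specified covariate, and that the treatment effect is the between-arm contrast at 24 months. The Baldini model would use the preoperative Baldini score, and each KOOS subscale its own preoperative value.

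An equivalent alternative is to model the preoperative value as a time-0 response with the arm means constrained equal. This needs a working correlation that lets that value inform the later visits; an independence structure would not.

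List any other covariates in advance, and label any adjustment beyond that list exploratory.

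The cost is a sentence or two and about one model degree of freedom. No new data are needed.

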## Discussion

The need to resurface the patella as part of a total knee arthroplasty (TKA) remains controversial[12, 37, 38]. Several prospective observational studies have shown that approximately 10% of patients are affected by significant patellofemoral complaints after TKA, despite patellar resurfacing[39–41].

Selective resurfacing may improve clinical success by identifying individuals who will benefit from resurfacing the patella[28]. In the present study all the included patients will have symptomatic patellofemoral OA as well as femorotibial OA. In our opinion this selection of patients provides a cohort that enables us to draw valid conclusions on patellar resurfacing with the use of the AGC total knee system. At our department the AGC^®^ Total Knee System is used. This knee prosthesis has excellent longevity with minimal wear despite a flat-on-flat geometry and posterior cruciate ligament retainment[42, 43]. Emerson et al.[43] showed a low rate of patellar failure in the AGC total knee system. Favourable component alignment together with unconstrained patellofemoral articulation most likely minimises patellofemoral stress. However, no specific patellofemoral scoring system was used in this study.

Baldini et al.[30] published a scoring system specifically designed to evaluate the patellofemoral joint before and after TKA. This scoring system is developed to determine function and pain, ranging from 0 to 100 points, and includes ratings for subjective and objective clinical aspects of the patellofemoral joint before and after TKA[30]. This dedicated patellofemoral scoring system will be used in our clinical trial to improve the accuracy of the clinical outcome assessment. Feller et al. performed a prospective study with a self-made specific score for the patellofemoral joint and arthritis. No significant difference between the two treatment groups (resurfacing versus non-resurfacing) for their patellar score was found. Although the study of Feller et al. has a similar design as the current study, they did not use a homogenous patient group: by contrast, in the present study all the included patients will have clinical and radiological femorotibial and patellofemoral OA[31].

The use of patient selection and a specific validated measurement tool allow us to expect to find a significant difference between the two groups that other prospective trials could not.

Most of these studies use established clinical knee scoring systems, such as the KSS[32] and the KOOS[33] as outcome assessments. The KSS is derived from clinical and radiological data and concentrates mainly on the surgeon’s view of the outcome, i.e. knee pain, joint deformity and knee motion[44–46]. Patients are more concerned with symptoms and functional limitations. It is well recognised that clinical outcome assessments and patient-related measurements evaluate different aspects of knee injury and knee OA. Weak correlations and frequent discordance are found when comparing clinical outcome assessments like radiographic findings and knee motion to patient-relevant outcomes such as pain, function and activity level[47–50].

A patient-reported outcome measure, specific for knee problems, will thus be used in this study. The KOOS used in our clinical trial is developed to assess patients' opinion about their knee and related problems[33]. The KOOS is a comprehensive instrument that includes five subscales assessing aspects of knee injury and knee OA considered important by patients. Most other instruments used for knee functional status combined items measuring different aspects into one score.

An additional aspect in studies assessing outcome of TKA is a discrepancy between patellofemoral symptoms and results obtained by conventional scoring and radiographic analysis[47–49]. Regular scoring systems focus mainly on tibiofemoral aspects and specific patellofemoral symptoms can be missed or underscored. Commonly used clinical outcome measures, such as the KSS, do not take into account subjective symptoms or objective data specifically arising from the patellofemoral joint. The Baldini score represents an essential complementary source of information to the existing KSS and KOOS scores since both scores do not specifically focus on patellofemoral problems.

Our study design is limited that results may not be applicable to other knee systems; especially posterior stabilized (PS) TKA. Alternative knee replacement designs may affect patellar kinematics differently. An in vitro study, however, showed similar quadriceps forces using CR or PS TKA systems[51]. To our knowledge no clinical trials have been published to confirm these findings.

Previous randomised controlled trials on the effectiveness of patellar resurfacing during primary TKA have included patients with knee OA regardless of patellofemoral complaints. This trial studies a selected cohort of patients receiving total knee replacement. All included patients have clinical and radiological patellofemoral OA besides symptomatic femorotibial OA. This is a difference compared to previous randomised controlled trials that have included patients with knee OA regardless of patellofemoral complaints.

Radiographic assessments used in clinical trials to evaluate the patellofemoral joint after TKA have remained basically unchanged for a number of decades, and do not accurately assess dynamic patellofemoral tracking following arthroplasty[52, 53]. Traditional radiographic assessment in a static unloaded position may not reproduce in vivo patellofemoral kinematics[54]. On the commonly used tangential patellar axial view radiographs, the patellar position relative to the trochlea is independent of fundamental dynamic and neuromuscular factors[55, 56]. The role of the quadriceps muscle in affecting the position of the patella relative to the femur must be considered. Additionally, patellar kinematics are influenced by the axial and rotational alignment of the lower limb[57]. Patients with patellofemoral problems following TKA typically experience anterior knee pain when the extensor apparatus is under load. Baldini et al.[30] developed a dynamic weight-bearing radiographic view that reproduces a semi-squatting positional setting which sufficiently loads the patellofemoral joint and involves the extensor apparatus. This view according to Baldini will be used in our clinical trial because it allows for better assessment of patellofemoral OA and patellar subluxation[29].

